## **10 Limitations**

Because we are opting to use data collected by auditors retrospectively up to one year after the enrolled patient’s initial operation, a key limitation in our study is recall bias. In a prior study assessing the roll of recall bias in evaluating complications after surgery in Ethiopian woman undergoing caesarean section, women were less likely to recall complications 6 months after their operation. As a result, our study cohort is more likely to remember complications at the end of the study, after the intervention, than at the beginning of the study before the intervention, in the control period. We believe this limitation is likely to bias us against finding a reduction in SSI associated with our outcome.

Additionally, loss to follow-up is a major limitation. Nearly half of patients could not be reached for their 30-day follow-up phone call by the auditors. However, in comparing demographic and clinical characteristics of these patients, they were not substantively different from our complete dataset. Sensitivity analyses to address loss to follow-up are described in Section 9.4.

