|                  |                          |       | Control period |   |   |   |   | Run-in period |          |          |      |            | Intervention period |          |   |          |   |   |      |   |  |

However, the overall N's for auditors in table 3 are smaller than those for data collectors. Table 4 shows the follow up rate for each group, by control or intervention condition. While the auditors yielded plausible SSI estimates, their follow-up rates were only 52% overall, which we attribute to the late date that they began and the challenging context that Ethiopia represents.

Table 4: 30-day follow-up rates by control and intervention condition, data collectors vs. auditors

| Cohort | Control condition      |                       |                |                       |                | Intervention condition |                       |                |                       |                |
|--------|------------------------|-----------------------|----------------|-----------------------|----------------|------------------------|-----------------------|----------------|-----------------------|----------------|
|        | N enrolled in facility | Data collectors       |                | Auditors              |                | N enrolled in facility | Data collectors       |                | Auditors              |                |
|        |                        | N with follow-up data | Follow-up rate | N with follow-up data | Follow-up rate |                        | N with follow-up data | Follow-up rate | N with follow-up data | Follow-up rate |
| 1      | 230                    | 223                   | 97%            | 111                   | 48%            | 772                    | 761                   | 99%            | 545                   | 71%            |
| 2      | 948                    | 904                   | 95%            | 422                   | 45%            | 1,704                  | 1,611                 | 95%            | 851                   | 50%            |
| 3      | 959                    | 911                   | 95%            | 600                   | 63%            | 975                    | 912                   | 94%            | 603                   | 62%            |

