| 4      | 2,002                  | 1,981                 | 99%            | 783                   | 39%            | 1,087                  | 947                   | 87%            | 607                   | 56%            |
| 5      | 1,576                  | 1,542                 | 98%            | 848                   | 53%            | 413                    | 361                   | 87%            | 222                   | 54%            |
| Total  | 5,715                  | 5,561                 | 97%            | 2,764                 | 48%            | 4,951                  | 4,592                 | 93%            | 2,828                 | 57%            |

30-day follow-up was lower among the auditors compared to the data collectors, with only 48% of patients followed up in the control condition and 57% in the intervention condition. Because the phone calls happened toward the end of the study, the calls in the intervention condition were much closer temporally the enrolled patients' operations compared to the calls to patients enrolled in the control condition, which made it difficult for the auditors to reach control-period patients.

While we recognize measurement problems with both the data collectors' and auditors' data, after consideration we decided to use the auditors' data for all follow-up measures, which include the primary outcome. We will construct some sensitivity analyses to test this decision, as described below. As we have also lost power within the study due to this loss to follow-up, we will add a sensitivity analysis using multiple imputation for the dependent variable to help recapture some statistical power, as described below.

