### 9.4 Sensitivity to loss to follow-up

First, we will construct a demographic table comparing the women who were followed up by the auditors against those who were not. This may identify some imbalances that may introduce bias.

Next, we will use multiple imputation methods to model the primary outcome with the total CS population. We will generate an imputed value and 95% CI for the OR of SSI in the intervention versus control period.

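### Loss to auditor follow-up: the table planned in SAP 9.4 has no stated split by condition and no outcome row, and the section 10 reassurance cannot show selection that differs by condition

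*Combined protocol and SAP*

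**What the plan says.** SAP section 6 restricts the primary population to cesarean patients with complete 30-day data from the auditors. Section 4.3 says of the auditors that "their follow-up rates were only 52% overall", and gives the split by condition: "with only 48% of patients followed up in the control condition and 57% in the intervention condition". It attributes the gap to control patients being called longer after surgery. Table 4 gives counts by cohort and condition.

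Section 9.4 (Sensitivity to loss to follow-up) plans two things. First, "we will construct a demographic table comparing the women who were followed up by the auditors against those who were not". No split by condition or cohort is mentioned, and no outcome is listed. Second, multiple imputation of the primary outcome in the total cesarean population. Neither the imputation variables nor a missingness assumption is stated. Section 4.3 gives the aim of the imputation as regaining power.

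Section 10 calls loss to follow-up a major limitation and then reports, in the past tense, that "in comparing demographic and clinical characteristics of these patients, they were not substantively different from our complete dataset".

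**The concern.** The complete-case odds ratio is biased by selection when the link between having an infection and being reached differs between control and intervention. Demographic similarity of reached and unreached women, taken over the whole study, does not bear on that directly. Selection that runs in opposite directions in the two conditions can cancel in a table that is not split.

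The sentence in section 10 adds two difficulties. It reports a conclusion from a comparison that, on its natural reading, is not the one planned in 9.4. It also sets a subgroup against a dataset that contains that subgroup, which shrinks any difference. A reader could take it as evidence that losing nearly half the follow-up did little harm to the primary result, which that comparison cannot supply.

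The SAP argues a conservative direction for recall bias (sections 4.2, 9.5 and 10). It offers no such argument for selection.

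**Working it through.** **1. Coverage, from the Table 4 counts (reached by auditors / enrolled).** The interval is d ± 1.96·√[p₁(1−p₁)/n₁ + p₂(1−p₂)/n₂], ignoring clustering by hospital.

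| Cohort | Control | Intervention | Change, points (95% CI) |
|---|---|---|---|
| 1 | 111/230 = 48.3% | 545/772 = 70.6% | +22.3 (15.1 to 29.5) |
| 2 | 422/948 = 44.5% | 851/1,704 = 49.9% | +5.4 (1.5 to 9.4) |
| 3 | 600/959 = 62.6% | 603/975 = 61.8% | −0.7 (−5.0 to 3.6) |
| 4 | 783/2,002 = 39.1% | 607/1,087 = 55.8% | +16.7 (13.1 to 20.4) |
| 5 | 848/1,576 = 53.8% | 222/413 = 53.8% | −0.1 (−5.5 to 5.3) |
| All | 2,764/5,715 = 48.4% | 2,828/4,951 = 57.1% | +8.8 |

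The SAP's 48%, 57% and 52% (5,592/10,666 = 52.4%) are reproduced. Nine of the ten cohort percentages match; cohort 5 control is printed as 53%. The N column of Table 3 totals 5,525, not 5,592, which gives 51.8% and still rounds to 52%. Coverage rises in cohorts 1, 2 and 4 and is flat in 3 and 5, so time since surgery does not by itself account for the pattern.

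**2. Overlap.** Let R and U be the means of a characteristic in reached and unreached patients, and f = 0.524 the proportion reached. The mean over everyone enrolled is A = f·R + (1−f)·U. Then U − A = −f·(R − U) = −0.524·(R − U), and R − A = (1−f)·(R − U) = 0.476·(R − U). If the complete dataset is everyone enrolled, a true 10-point difference between reached and unreached appears as 5.2 points.

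**3. Cancellation when conditions are not separated (illustrative inputs).** Take a characteristic with 60% prevalence in each condition. Reached minus unreached is +10 points in control and −10 in intervention.
- Control: reached 60 + 0.516×10 = 65.2%, unreached 60 − 0.484×10 = 55.2%.
- Intervention: reached 60 − 0.429×10 = 55.7%, unreached 60 + 0.571×10 = 65.7%.
- Gap between conditions among the reached: 55.7 − 65.2 = −9.5 points.
- Weighted by the counts in step 1, all reached 60.4% and all unreached 59.6%, a difference of 0.8 points.
- Unreached minus everyone: −0.4 points.

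**4. Effect on the odds ratio.** Within a condition, the odds of infection among the reached equal the true odds times r = P(reached | SSI) / P(reached | no SSI). So the observed OR = true OR × r(intervention)/r(control). Illustrative values:
- r = 1.2 in control, 1.0 in intervention: 1/1.2 = 0.83.
- r = 1.0 in control, 1.2 in intervention: 1.2.
- r = 1.1 and 0.9: 0.9/1.1 = 0.82.
- r = 0.8 and 1.0: 1/0.8 = 1.25.

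For scale, the protocol's example of 12% falling to 9% is an OR of (0.09/0.91)/(0.12/0.88) = 0.73.

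**5. Data already held on the unreached (Table 4).**
- Control: 5,715 − 2,764 = 2,951 unreached; 5,715 − 5,561 = 154 have no data-collector result. At least (2,951 − 154)/2,951 = 94.8% of the unreached have one.
- Intervention: 4,951 − 2,828 = 2,123 unreached; 4,951 − 4,592 = 359 have none. At least (2,123 − 359)/2,123 = 83.1% have one.

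Section 4.1 also describes the in-hospital infection data as robust.

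**The case against.** The SAP does more than tabulate demographics. It plans multiple imputation over all cesarean patients. Section 8.1 compares control with intervention in each study population, including the followed-up one. Section 9.3 leaves out each hospital in turn. It publishes coverage by cohort and condition and names the loss as a major limitation.

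The words *complete dataset* may mean patients with complete data, since section 6 defines the primary population by complete auditor follow-up. The comparison would then be unreached versus reached, with no overlap. Unequal coverage is also not bias in itself: month effects and a cohort random effect are in the primary model, so a reach–infection link that varied only by calendar month or only by cohort would largely be absorbed. Table 4 counts all enrolled patients, not cesarean patients. The reach ratios in step 4 are assumed.

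Most of this stands and limits the point. A reader might infer that the SAP checks follow-up only with a table pooled over conditions, so that differential selection must go unseen. The documents do not support that. Section 9.4 is silent on the split rather than committed to pooling, other analyses exist, and Table 4 already displays unequal coverage. Nor do they support inferring that the primary odds ratio is biased, or in which direction.

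What the objection does not remove:
- Section 8.1 could show imbalance between conditions among the reached, but could not separate selection from a change in case mix, because no by-condition table of all cesarean patients is planned.
- The imputation cannot be judged without its variables and assumption.
- On either reading of section 10, the comparison is not made within condition and contains no outcome.

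**Conclusion.** The point holds in a limited form. Follow-up that defines the primary population differs by condition and unevenly by cohort. The stated diagnostic specifies neither a split by condition nor an outcome row, and section 10 draws reassurance from a comparison that cannot address selection differing by condition. The 0.52 dilution is exact algebra, but applies only if the complete dataset means everyone enrolled.

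The possible distortion of the odds ratio, 0.83 or 1.2 in the simplest cases, is illustrative. It assumes reach ratios that the documents do not give, applies to the crude odds ratio, and can go either way. Coverage among cesarean patients alone is not reported and may differ from Table 4.

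**What to change.** In section 9.4, for the total cesarean population:
- Show reached versus not reached separately for control and intervention, with coverage and covariates also by cohort.
- Add two outcome rows: infection recorded on the ward, and infection recorded at the data collectors' day-30 call.
- Report the reach ratio by infection status within each condition, and the ratio of the two, as an indicative selection-bias factor for the odds ratio. Do not split these ratios by cohort; events would be too few.
- State the imputation model and its missingness assumption, and include condition, cohort, month, ward infection and data-collector infection.

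In section 10, replace the comparison with the complete dataset by this result, and remove the statement of no substantive difference until the result is available.

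The cost is one extra table from data already collected, plus SAP wording. The bias factor would be indicative, not definitive: the SAP itself judges data-collector infections under-recorded (sections 3.2 and 4.2), ward records miss the majority of infections because these arise after discharge (section 4.1), and a crude factor does not separate condition from calendar month.
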